**Content**

1. Summary of the research plan 3
2. Research plan 4
   1. Current state of research 4
   2. Theoretical underpinning of proposed research plan 5
   3. Aims of the study 5
3. Methods 6
   1. Study design and data analysis 6
   2. Data analysis and sample size estimation 6
   3. Recruitment and randomisation 7
   4. Inclusion and exclusion criteria 8
   5. Explanations of the used variables 8
4. Duties of the investigator and quality management 11
5. Ethical Aspects and Quality Assurance 11
6. Documentation of the data, quality control and quality assurance 12

6.1 Budget 12

1. Signature of the principal investigators 12
2. References 13
3. Attachment: Plan of the social support intervention 17
4. **Summary of the research plan**

Psychosocial stress is a potent activator of the hypothalamus–pituitary–adrenal (HPA) axis. While neuroendocrine stress responses are essential for the maintenance of homeostasis, evidence suggests that excessive activation of the HPA axis constitutes a risk for disease and psychopathology. Previously, our group has shown that cognitive-behavioural as well as resource-focussed stress management trainings effectively reduce the activation of the HPA axis under stress in healthy subjects. However, these interventions focus on fight-or-flight type responses to stress.

Numerous studies demonstrated the essential importance of interpersonal ties, social support and social integration for health, wellbeing and even survival, which are mediated to a large extent by direct effects of social support on biological parameters of stress reactivity, including autonomous nervous system markers as well as immune and neuroendocrine markers. Although the positive effects of social support are well supported as well as long accepted, a stress management intervention based on social support has not been designed and tested so far.

Therefore, the purpose of the present study is to develop and evaluate the effects of social support-based stress management training on psychological wellbeing and endocrine stress responses under acute psychosocial stress among healthy young subjects.

1. **Research plan**

***2.1 Current state of research***

Psychosocial stress can be conceptualized as incongruence between the abilities and needs of a person and the environment. At the individual level, psychosocial stress is the result of a cognitive appraisal of what is at stake and what can be done about it (Lazarus, 2005; Lazarus & Folkman, 1984). It is assumed that the result of this subjective appraisal influences the emotional, behavioural, and biological responses to stress.

Regarding biological responses to psychosocial stress, hormones of the hypothalamus pituitary adrenal (HPA) axis have been examined extensively. Although the activation of the HPA axis in response to stress and its effects on cardiovascular, immune, and metabolic as well as emotional, behaviour, and cognitive processes helps to maintain equilibrium during and after stress (Sapolsky, Romero, & Munck, 2000), extensive and/or long- standing release of HPA axis hormones has been shown to have detrimental effects on somatic and emotional well-being (McEwen, 1998; Seeman, McEwen, Rowe, & Singer, 2001). Beside genetic (Wüst et al., 2004), endocrine (Kirschbaum, Kudielka, Gaab, Schommer, & Hellhammer, 1999), and habitual (Kirschbaum, Wüst, & Strasburger, 1992) factors, situation-specific anticipatory cognitive appraisal, but not general personality variables, substantially account for the extent of the biological response in the face of stress (Gaab, Rohleder, Nater, & Ehlert, 2005). Particularly the perception of threat to the social self that is judged as uncontrollable is a major situational trigger of the HPA axis activation in response to stress (Dickerson & Kemeny, 2004).

While uncontrollable social evaluation was shown to be one of the strongest stressors (Dickerson & Kemeny, 2004), positive social interactions are essential to physiological and psychological wellbeing. Being integrated in close social relationships or perceiving that social support would be available in case of need has considerable positive consequences for health and even survival (Holt-Lunstad, Smith, & Layton, 2010), with effect sizes equalling or exceeding those of well-established behavioural factors such as smoking cessation, exercise, and abstinence from alcohol. Both the direct positive effect of social support and integration on various health parameters as well as the reduction of the incidence or frequency of stress are discussed as putative mechanisms of stress-protective effects by social support (Cohen & Wills, 1985; Cohen, 1988).

Beside the long-term health outcomes, direct effects of social support on acute stress reaction were intensively investigated in the last decades. Instructed social support reduces autonomic nervous system activation to stress measured on cardiovascular parameters. This effect is moderated by quality of the interaction, and was shown to be the strongest for non-evaluative positive emotional support (Allen, 2002; Gerin, Pieper, Levy, & Pickering, 1992; Kamarck, Manuck, & Jennings, 1990; Lepore, Allen, & Evans, 1993). Similarly, reduction of endocrine stress response (lower salivary free cortisol levels) to a standardized laboratory stress test TSST was observed both for men and women (Kirschbaum, Pirke, & Hellhammer, 1993). Interestingly, men benefited more from verbal support by their partner, whereas women from non-evaluative nonverbal support expressed in touch, hugs or smiling, while the verbal support by their partner rather increased the cortisol levels instead (Ditzen et al., 2007; Heinrichs, Baumgartner, Kirschbaum, & Ehlert, 2003).

Taylor et al. (2000) postulated that the stress-protective effects of social support are differently utilized by men and women. Beside the fight-or-flight behaviour that may characterize the primary physiological response to stress for both males and females, behaviourally, females’ responses are more marked by a pattern of tend-and-befriend. Tending is defined as nurturing activities to protect the self and offspring, promote safety and reduce distress; and befriending as the creation and maintenance of social networks that may aid in this process. In accord to this hypothesis, interpersonal stressors like social rejection elicited higher free cortisol increases in women that in men, whereas situations involving intellectual inferiority and performance failures were perceived as more stressful by men (Stroud, Salovey & Epel, 2002).

- 1. ***Theoretical underpinning of proposed research plan***

A number of studies have shown that cognitive–behavioural stress management (CBSM) effectively reduces basal cortisol levels and/or psychological morbidity shortly after the intervention in clinical as well as nonclinical populations (HIV: Berger et al., 2008, Antoni et al., 2000, and Cruess et al., 1999; breast cancer: Cruess et al., 2000; athletes: Perna, Antoni, Kumar, Cruess, & Schneiderman, 1998). Also, in healthy participants, CBSM was observed to attenuate cortisol responses to a standardized stress test 2 weeks as well as 4 months after training (Gaab et al., 2003; Hammerfald et al., 2006).

The mentioned interventions aim to address explicit levels of self-evaluation. Individuals reflect on their experiences, evaluate the contents of consciousness, and introspect about the causes and meanings of stressful situations.

In most cases the studies were conducted with only male participants, to exclude the methodological difficulty that the intensity of endocrine response in females of reproductive age depends on the phase of the cycle and use of oral contraceptives (Kirschbaum et.al., 1999). The CBSM intervention was effective for men (Gaab et al., 2003), and when both sexes were participating, the effect of cognitive training for women was weaker (Hammerfald et al., 2006). Thus, it can be speculated that these types of stress management address rather the fight-or-flight response and might be in general more beneficial for men that for women.

Previous research indicates the essential direct effects of social support on stress reactivity and the presumably higher importance of interpersonal processes for women. The goal of this study is to develop and evaluate a tend-and-befriend type stress management intervention. Since we hypothesize, that social support intervention targets the postulated, primarily feminine, tend and befriend stress coping mechanism, its efficacy will be tested on female subjects.

***2.3 Aims of the study***

In summary, the majority of studies on the effects of stress management training are based on a problem-oriented fight-or-flight type of stress coping. The goal of this study is to develop a tend-and-befriend based stress management intervention and test its effects on acute neuroendocrine, psychophysioloigcal as well as subjective stress responses as well as on psychological well-being, using a methodological approach similar to that used in previous CBSM studies (Gaab et al., 2003; Hammerfald et al., 2006, Storch et al., 2007).

1. **Methods**

***3.1 Study design and data analysis***

This study is an experimental study with parallel groups. Subjects are randomized into the two conditions: Treatment condition, thus receiving tend-and-befriend training (TBT) *before* the TSST; control conditions = waitlist controls receiving tend-and-befriend training (TBT) after the termination of the study. Two weeks after the participants of the treatment condition have received the tend-and-befriend training (TBT), all participants of the treatment as well as the control condition will undergo a standardized psychosocial stress test, the Trier Social Stress Test (TSST, Kirschbaum et al., 1993). The study variables are displayed in Table 1, the flow through the study is shown in Table 2.

Table 1. Study variables

| Variables | Description | Time |
| --- | --- | --- |
| Independent Variable | Tend-and-befriend training (TBT) and waitlist control condition (WL-CC) | TBT two weeks before TSST, WL-CC after termination of study |
| Primary outcome | Cortisol and alpha-amylase | 9 measurements before, during and after TSST |
| Secondary outcomes | Psychophysiological parameters (heart rate, electrodermal activity, electrocardiography, electromyography, respiratory activity and skin temperature) | Repeated assessment before, during and after TSST |
|  | Questionnaires (PASA, STAI X-1, STAI X-2, PSS, FSozU, BFW/E, ASS-SYM) | TSST: PASA, STAI X-1  Baseline, post and follow-up: STAI X-2, PSS, FSozU, BFW/E, ASS-SYM |

***3.2 Data analysis and sample size estimation***

Multivariate analyses of covariance and variance for repeated measures will be computed to analyse endocrine and psychophysiological stress responses as well as pre-post changes of psychometric scores between groups, controlling for differences in baseline levels when indicated. Regression analysis will be used to assess associations between psychological and cortisol parameters. For cortisol and psychophysiological parameters, areas under the response curve will be calculated with respect to increase (AUCi) and ground (AUCg), using the trapezoidal method as an indicator for the integrated biological and physiological response in the TSST (Pruessner, Kirschbaum, Meinlschmid, & Hellhammer, 2003). Data will be tested for normal distribution and homogeneity of variance using the Kolmogorov-Smirnov test and Levene’s test before statistical procedures were applied. Based on previous own studies (Gaab et al., 2003, Hammerfald et al., 2006, Storch et al., 2007), we expect a large multivariate effect size (f^2^=0.35), Therefore, the optimal total sample size of N = 48 to detect an expected large effect size of f2 = 0.35 (representing a large effect size) with a power = 0.85 and α = 0.05 was calculated a priori with the statistical software G-Power (Buchner et al., 1997). For all analyses, significance level is α = 5%. All analyses are performed according to the principle of intention to treat, with last observations carried forward when follow-up data were missing.

*Table 2: Flow through the study*

|  | TBT | WL-CC | |
| --- | --- | --- | --- |
| Baseline assessment | Advertisement with bulletins and BAPS  Information about study procedure on BAPS, screening for inclusion- and exclusion criteria on BAPS  STAI X-2, PSS, FSozU, BFW/E, ASS-SYM | | |
| Intervention | TBT | | - |
| Stress test | TSST  Assessment of 9 saliva samples -30, -20, -10, 0, 10, 20, 30, 45 and 60 min (with 0 min being directly post-TSST) for salivary free cortisol and alpha-amylase.  Continuous assessment of psychophysiological parameters (heart rate, electrodermal activity, electrocardiography, electromyography, respiratory activity and skin temperature)  Questionnaires: PASA (once), STAI X-1 | | |
| Post assessment | STAI X-2, PSS, FSozU, BFW/E, ASS-SYM | | |
| Follow-up assessment | STAI X-2, PSS, FSozU, BFW/E, ASS-SYM | | |

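### The repeated-measures MANOVA/MANCOVA named for the nine-sample curves by default drops a woman with one missing sample, and the only missing-data rule does not sensibly cover saliva samples

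*Protocol*

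**What the plan says.** Section 3.1, Table 1, makes cortisol and alpha-amylase the primary outcome, with "9 measurements before, during and after TSST". Table 2 in section 3.2 gives the schedule: "Assessment of 9 saliva samples -30, -20, -10, 0, 10, 20, 30, 45 and 60 min", where 0 min is the end of the test.

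The method in section 3.2 is: "Multivariate analyses of covariance and variance for repeated measures will be computed to analyse endocrine and psychophysiological stress responses". For cortisol and the psychophysiological signals, the section adds trapezoidal areas under the curve, with respect to increase (AUCi) and to ground (AUCg).

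The analysis principle is: "All analyses are performed according to the principle of intention to treat". The same sentence holds the only missing-data rule, which carries the last observation forward where follow-up data are absent. Elsewhere in the protocol, follow-up is a questionnaire assessment. Table 2 lists it as a row separate from the stress test, and section 3.5 dates it four weeks after the intervention.

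The sample size is stated as "the optimal total sample size of N = 48 to detect an expected large effect size of f2 = 0.35", "with a power = 0.85 and α = 0.05 was calculated a priori". No allowance for dropout or lost samples accompanies it. Section 3.3 lets women withdraw at any time, and the section on ethical aspects lets them stop the stress test at any time.

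**The concern.** The classical form of the named method works on a complete vector of responses per woman. If one of the nine values is absent and nothing replaces it, the other eight are discarded with it. The primary comparison would then run on women selected by the completeness of their samples, while the same paragraph promises intention to treat for all analyses.

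Two things are at stake. One is power, because a small loss per sample can become a larger loss of women, and N = 48 has no stated margin. The other is selection. A woman who stops the stress test early may do so because of how she responds to it, so the complete subset need not resemble the randomised groups.

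**Working it through.** **1. Does the missing-data rule close the gap?** There are two readings.

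- Narrow, following the protocol's own use of the term: follow-up means the four-week questionnaires. The rule then says nothing about saliva samples.
- Broad: any later value counts as follow-up. A missing 0 min sample would take the -10 min value, so a pre-stress level would stand in for the first post-stress one. A missing 45 min sample would take the 30 min value and hide part of the recovery. The -30 min sample has no predecessor, and a missed session has nothing to carry. The cortisol AUCi and AUCg would inherit the distortion.

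Neither reading gives a sound rule for these samples.

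**2. Reproducing N = 48.** Inputs from section 3.2: f² = 0.35, α = 0.05, power 0.85. The test is a noncentral F with λ = f² × N and degrees of freedom (u, N − u − 1). This is G*Power's omnibus regression test and equally a two-group multivariate test with u responses. The protocol does not state u.

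| u | Smallest N for power 0.85 | Power at N = 48 |
|---|---|---|
| 4 | 44 | 0.892 |
| 5 | 47 | 0.860 |
| 6 | 51 | 0.827 |
| 8 | 57 | 0.762 |

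Only u = 5 comes within two of 48. There λ = 0.35 × 48 = 16.8 with (5, 42) df. A 5-df test in a model with 6 to 11 predictors gives exactly 48. This basis is used below because it lies closest to the protocol's own figure.

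**3. Complete women.** The protocol gives no loss rate, so q, the chance that one sample is missing, is assumed over a range. If losses are independent, the complete share is (1 − q)^9.

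| q | (1 − q)^9 | Complete of 48 | Power, u = 5 |
|---|---|---|---|
| 0 | 1.000 | 48 | 0.860 |
| 0.5% | 0.956 | 46 | 0.840 |
| 1% | 0.914 | 44 | 0.818 |
| 2% | 0.834 | 40 | 0.766 |
| 3% | 0.760 | 36 | 0.704 |
| 5% | 0.630 | 30 | 0.589 |

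Losing exactly one woman (N = 47) gives 0.850, a cost of one point.

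**4. The opposite assumption.** If all loss came as whole sessions, the women lost would be q × 48. At 5% that is 0.05 × 48 = 2.4, leaving about 46 and power 0.840. The independent figures are therefore the unfavourable end of the range. Loss of whole sessions is also the kind that no analysis of available samples can recover.

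**The case against.** The strongest reply is that the protocol never prescribes a complete-case analysis. A reader might infer that it does, but no section says so. Listwise deletion is the default of the named method, and a MANOVA can be run on filled data. How to fill a single missing sample is detail that an analysis plan, not shown here, could supply. This stands as far as it goes. What remains is that the protocol itself pairs a complete-vector method with a promise covering all analyses and a missing-data rule that does not fit these samples.

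A simple fill would also help. In a simulation with 24 women per arm, correlation 0.85 per 10 min, an assumed curve shape, f² = 0.35 and the 8-df multivariate test, linear interpolation gave power 0.745 at 2% loss and 0.729 at 5%. With complete data power was 0.763, and with complete cases only it was 0.64 and 0.44. So the named method could be kept with a fill rule. The mixed model is preferable because it needs no invented values, but it is not the only remedy.

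Three further inferences are tempting and not supported:

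- **Starting from power 0.76.** The 8-df group-by-time test has power 0.762 at N = 48 with nothing missing. The gap to 0.86 is a matter of degrees of freedom, separate from lost samples, and should not be counted here.
- **Extending the point to the psychophysiological signals.** These are recorded continuously and edited before analysis. If they are summarised by period, a lost stretch need not leave an empty cell, and the protocol reports no such loss.
- **Claiming that a mixed model keeps all the power.** A simulated likelihood test on incomplete data gave 0.774 to 0.779, above the complete-data 0.762. Missing data cannot raise power. That test's type I error was 0.063 to 0.067, and the Kenward-Roger version recommended below was not simulated.

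**Conclusion.** The point holds as a mismatch within section 3.2 that is cheap to remove. The stated method, intention-to-treat promise and missing-data rule do not fit together for the nine-sample primary outcomes.

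The size is conditional. It rests on an assumed loss rate, on independent loss, on complete-case handling and on the 5-df basis. Under these, 1%, 2% or 5% loss takes power from 0.86 to about 0.82, 0.77 or 0.59. The cost becomes material from roughly 1 to 2% of samples upwards, and is smaller if losses cluster within women.

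A reader might conclude that the primary analysis breaks intention to treat or is underpowered because of missing samples. The protocol does not support that, since it gives neither a loss rate nor an exclusion rule. It is a change that should be made, not a demonstrated failure of the primary analysis.

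**What to change.** In section 3.2:

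1. Analyse the cortisol and alpha-amylase curves with a likelihood-based linear mixed model: time as nine categories, arm, arm-by-time, a prespecified covariance structure and Kenward-Roger degrees of freedom. Fit it to every available sample of every randomised woman with stress-test data.
2. State that carrying the last observation forward does not apply to stress-test samples.
3. For AUCi and AUCg, bridge a single interior missing sample by the trapezoid between its neighbours. State what happens when the first, the last or two adjacent samples are missing, because the bridge does not cover these.
4. Say in the intention-to-treat sentence that randomised women with no stress-test data cannot enter this analysis, and report their number by arm.

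The cost is analysis wording: a covariance structure and a degrees-of-freedom method must be fixed in advance. An unstructured 9 × 9 covariance has 9 × 10 / 2 = 45 parameters, which is heavy for 48 women, so a fallback structure should be named. With complete data the test is essentially the planned one. The model assumes that missingness depends only on observed data, which may fail for women who stop the test early.

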***3.3 Recruitment and randomisation***

Participants will be recruited via the online recruitment system of the Department of Psychology (BAPS-Sona, http://baps.sona-systems.com) and in lectures at the University of Basel. Subjects interested in participating in the study can sign up by e-mail. All interested subjects will be screened for inclusion and exclusion criteria and be informed verbally about the goal and the procedure of the study by telephone interview. In case of willingness to participate in the study, subjects receive a written description of the study aims, theoretical background as well as employed psychotherapeutic methods and experimental procedures (i.e. randomization and TSST) as well as the written informed consent and the a link to the baseline assessments (see below).

Upon receipt of the signed written informed consent and the filled-out questionnaires, participants will be randomized through individual assignment codes in properly concealed between black sheets, stored in sequentially numbered envelopes. After randomization, participants will be informed about study dates, thus dates for the tend-and-befriend training (TBT) and the TSST. The study participation is voluntary. Subjects can end their participation anytime and without any reason and disadvantage. The participation can be ended by the study staff when participation might have detrimental effects (e.g. participants appears to be in psychosocial crisis), the study design is not followed and in case of adverse events. The participation in the study must be ended if in retrospect the inclusion criteria do not apply to the subject or if one exclusion criterion is met.

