- *The State-Trait Anxiety Inventory* (STAI, [Laux, Glanzmann, Schaffner, & Spielberger, 1981](#_ENREF_22)): This instrument assess not only state but also trait anxiety. The STAI X-1 consists of 20 statements and the answers to these are used to judge a patient's degree of anxiety at a specific time (state anxiety) and is completed prior to the introduction to the TSST, just before, and 1 hour after the TSST. The STAI X-2 form consists of a different set of 20 statements, and the answers to these are used to calculate a patient's underlying (trait/personality) degree of anxiety. STAI X-2 is administered at the baseline assessment, directly after the intervention and at the follow-up assessment, 4 weeks after the intervention. Each statement in both STAI is rated on a 4-point scale according to the patient's agreement with that statement. The overall score for STAI ranges from a minimum of 20 to a maximum of 80; STAI scores are commonly classified as “little or no anxiety” (20–37), “moderate anxiety” (38–44), and “extreme anxiety” (45–80). The duration is defined as 3 to 6 minutes per scale.
- A German translation of the *Perceived Stress Scale* (PSS, Cohen et al., 1983) will be used to assess the degree to which situations experienced during the last few days are perceived as stressful. Items in the PSS are designed to assess how predictable, uncontrollable, and overloading participants find their lives at the moment. The PSS is administered at the baseline assessment, directly after the intervention and at the follow-up assessment, 4 weeks after the intervention.
- *Fragebogen zur Sozialen Unterstützung (*ll, Fydrich, Sommer & Brähler, 2007, 22 items version) will be used to assess the subjective availability of resources from the participants’ social network. The questionnaire covers following dimensions (1) emotional support, (2) practical support, (3) social integration, (4) burden coming from social network, as well as (5) reciprocity, (6) availability of a trusted person, and (7) satisfaction with the social support. Each statement is rated on a 5-point scale according to the patient's agreement with that statement. The FSozU is administered at the baseline assessment, directly after the intervention and at the follow-up assessment.

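### PASA and STAI X-1 have no pre-training value, and section 3.2 names no pre-randomisation covariate for them although baseline STAI X-2 is at hand: a possible loss of precision on secondary outcomes

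*Protocol*

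**What the plan says.** Section 2.3 of the protocol includes subjective stress responses among the aims, and Table 1 (section 3.1) lists PASA and STAI X-1 among the secondary outcomes. Table 1 gives their timing as "TSST: PASA, STAI X-1", and Table 2 has PASA once, in the stress-test row. The TSST follows the training by two weeks.

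The trait form of the same inventory is timed differently (section 3.5): "STAI X-2 is administered at the baseline assessment, directly after the intervention and at the follow-up assessment, 4 weeks after the intervention". Section 3.3 puts the baseline questionnaires ahead of allocation: "Upon receipt of the signed written informed consent and the filled-out questionnaires, participants will be randomized".

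The analysis paragraph in section 3.2 covers endocrine and psychophysiological responses "as well as pre-post changes of psychometric scores between groups". It provides for control of baseline differences only where indicated and names no covariate. It does not mention PASA or STAI X-1 by name.

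**The concern.** The only adjustment rule in section 3.2 refers to baseline levels, and these two outcomes have none from before training. The nearest candidate is the first STAI X-1 reading, taken before the TSST is introduced. That reading comes after randomisation and two weeks after training. Adjusting for it as if it were a pre-treatment value would remove any training effect already present when the woman arrives.

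Meanwhile a score that allocation cannot have affected, and that plausibly relates to anxiety and threat appraisal in the test, is already collected and is not assigned to this use. In a trial of 48 women, precision on the subjective outcomes is worth having when it needs no new data. A rule that adjusts only when indicated does not secure that gain, because the gain comes from the correlation between covariate and outcome and not from an observed imbalance.

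**Working it through.** **The protocol's own figure.** Section 3.2 gives an "optimal total sample size of N = 48" for f² = 0.35, "with a power = 0.85 and α = 0.05 was calculated a priori". The number of predictors or dependent variables, k, is not stated, so the figure cannot be reproduced from the stated inputs alone. Using noncentral F with λ = 0.35·N and df = k, N − k − 1, the required N is 28 for k = 1, 44 for k = 4, 47 for k = 5 (power 0.860 at N = 48) and 51 for k = 6. So k = 5 comes close. The point here does not depend on this; it uses only N = 48.

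**Inputs.**
- n = 48/2 = 24 per arm. Equal allocation and no dropout are assumed; neither is stated.
- α = 0.05 (section 3.2), taken as two-sided.
- Standardised effect d = 0.6: assumed.
- r, the within-arm correlation of baseline STAI X-2 with the outcome: not in the documents, so shown as a range.

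**Formulas, in SD units.**
- Unadjusted: SE₀ = √(2/n) = √(2/24) = 0.2887, df = 46.
- ANCOVA: SE₁ = √[(1 − r²)·(2/n)·(1 + 1/(2n − 4))], df = 45. The last factor, 1 + 1/44 = 45/44, is the small-sample cost of estimating the covariate slope.
- Power from the noncentral t distribution with noncentrality d/SE.

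**Unadjusted.** Noncentrality 0.6/0.2887 = 2.078; critical t (46 df) 2.013; power 0.53.

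**Adjusted, d = 0.6.**

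| r | r² | SE₁ | SE₁/SE₀ | d/SE₁ | power |
|---|---|---|---|---|---|
| 0 | 0 | 0.2919 | 1.011 | 2.055 | 0.52 |
| 0.1 | 0.01 | 0.2905 | 1.006 | 2.066 | 0.525 |
| 0.2 | 0.04 | 0.2860 | 0.991 | 2.098 | 0.54 |
| 0.3 | 0.09 | 0.2785 | 0.965 | 2.154 | 0.56 |
| 0.5 | 0.25 | 0.2528 | 0.876 | 2.373 | 0.64 |
| 0.7 | 0.49 | 0.2085 | 0.722 | 2.878 | 0.80 |

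**Break-even.** SE₁ = SE₀ when (1 − r²)·45/44 = 1, so r² = 1/45 and r ≈ 0.15. Below that, adjustment costs a little: at r = 0 power falls from 0.53 to 0.52.

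**Other effect sizes.** At d = 0.5, power is 0.40 unadjusted and 0.40, 0.42, 0.49 and 0.65 for r = 0.2, 0.3, 0.5 and 0.7. At d = 0.8 it is 0.77 unadjusted and 0.78, 0.80, 0.87 and 0.96. The difference detectable with 85% power is 0.884 SD unadjusted, and 0.876, 0.853 and 0.774 SD for r = 0.2, 0.3 and 0.5.

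**Which outcomes this covers.** The calculation fits a single value per woman: each PASA scale, or her overall STAI X-1 level. For change within the session, write Y(time) = b·trait + other terms. If the trait score shifts every reading by the same amount, then Y(later) − Y(first) contains b·trait − b·trait = 0. Adjustment then has little to remove from the group-by-time contrast.

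**The case against.** The strongest objection is that the protocol is silent here rather than wrong. A covariate for two secondary questionnaires can be set in an SAP that is not shown. The phrase on pre-post changes most naturally describes the questionnaires given at baseline, post and follow-up. Analysis of covariance is already planned, and nothing in 3.2 forbids STAI X-2 as a covariate. All of this stands. A reader might infer that the plan leaves STAI X-2 unused, or commits to comparing PASA and STAI X-1 unadjusted. The text supports neither: STAI X-2 is analysed as an outcome, and how the other two are compared is not written down. What survives is that the one adjustment rule 3.2 does fix is conditional and refers to baseline levels these outcomes lack.

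Second, the gain rests on an assumed correlation. The protocol offers no evidence that trait anxiety predicts appraisal or state anxiety in the TSST. Section 2.1 even says that general personality variables do not account substantially for the response. That sentence concerns the biological response, so it is not decisive, but it lends no support either. The protocol also plans for a large effect. If f² = 0.35 held for a single outcome, d = 2√0.35 = 1.18 and unadjusted power would already be 0.98, leaving little to gain.

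Third, a reader might infer that a chance imbalance in trait anxiety would bias the arm difference. It would not. Only the part proportional to the trait-outcome association enters any one estimate, randomisation keeps the comparison unbiased, and the type I error already allows for such imbalance.

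**Conclusion.** The point holds as a minor, optional gain in precision. PASA and STAI X-1 have no pre-training value, the baseline clause in 3.2 therefore gives them no usable adjustment, and baseline STAI X-2 is not named for that purpose.

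The benefit ranges from nothing to substantial. At d = 0.6 the change in power lies between a loss of about 0.01 (r near 0) and a gain of 0.27 (0.80 − 0.53, at r = 0.7); at r = 0.3 it is 0.03 and at r = 0.5 it is 0.11. The upper end should not be read as the expected gain. The figures rest on 24 women per arm, no dropout, a two-sided test, an assumed effect and an assumed correlation. They apply to PASA and to the overall STAI X-1 level, with little gain expected for the STAI X-1 group-by-time contrast. Neither the validity of the trial nor its primary outcomes are affected.

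**What to change.** Add to section 3.2, for example: *The PASA scales and the overall STAI X-1 level in the TSST session are compared between arms by ANCOVA, with the baseline STAI X-2 score, collected before randomisation, as a covariate fixed in advance and used regardless of observed imbalance. The first in-session STAI X-1 reading is not treated as a pre-treatment baseline.*

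The overall STAI X-1 level needs a definition, and for that the number of readings must be settled. The TSST description in section 3.5 has four state-anxiety assessments (with the basal sample, during preparation, directly after, and at 60 minutes), while the STAI description in the same section has three, without the one directly after. The two should be reconciled.

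The cost is one sentence and one degree of freedom. No new data are needed, and because randomisation follows receipt of the completed questionnaires, the covariate should be available for essentially every randomised woman. If the correlation turns out below about 0.15, power falls by about 0.01 at most.
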